## Abstract

**Background:**

General Practice Optimising Structured Monitoring to Improve Clinical Outcomes in Type 2 Diabetes (GP-OSMOTIC) is a multicentre, individually randomised controlled trial aiming to compare the use of intermittent retrospective continuous glucose monitoring (r-CGM) to usual care in patients with type 2 diabetes attending general practice. The study protocol was published in the British Medical Journal Open and described the principal features of the statistical methods that will be used to analyse the trial data. This paper provides greater detail on the statistical analysis plan, including background and justification for the statistical methods chosen, in accordance with SPIRIT guidelines.

**Objective:**

To describe in detail the data management process and statistical methods that will be used to analyse the trial data.

**Methods:**

An overview of the trial design and primary and secondary research questions are provided. Sample size assumptions and calculations are explained, and randomisation and data management processes are described in detail. The planned statistical analyses for primary and secondary outcomes and sub-group analyses are specified along with the intended table layouts for presentation of the results.

**Conclusion:**

In accordance with best practice, all analyses outlined in the document are based on the aims of the study and have been pre-specified prior to the completion of data collection and outcome analyses.

**Trial registration:**

Australian New Zealand Clinical Trials Registry, ACTRN12616001372471. Registered on 3 August 2016.

## Background

The prevalence of type 2 diabetes (T2D) is rapidly increasing and is expected to reach close to 600 million worldwide by 2030 [1]. Close to 1.3 million Australians have been diagnosed with diabetes, with over 85% having T2D [2].

Early management and maintenance of glycaemic (blood glucose) levels through lifestyle modification and pharmacological treatments can reduce the likelihood of diabetes-related complications [3]. Glycated haemoglobin (HbA1c) is an index of average blood glucose level over the preceding 12 weeks and can be measured in mmol/mol or % [4]. HbA1c can be converted from one unit to the other using the relationship mmol/mol = 10.93 × HbA1c (%) – 23.5 [5]. Current guidelines base treatment intensification recommendations on HbA1c levels [6, 7]. The general HbA1c target in Australia is 53 mmol/mol (7%) [8]; however, the Australian Diabetes Society recommends that targets should also take into consideration factors such as age, duration of diabetes, and risk of hypoglycaemia [9]. Clinical care in general practice can help people with T2D achieve HbA1c targets [10] through adopting an evidence-based “treat-to-target” approach (step-wise treatment intensification through changes to lifestyle, medication doses, and/or prescription of additional medications). However, the majority of people with T2D have an HbA1c above their target level and treatment intensification is commonly delayed beyond clinical need [11]. One contributor to this may be that general practitioners (GP) and people with T2D lack an acceptable, feasible, simple, reliable, and effective method for identifying detailed day-to-day blood glucose patterns (glucose profiles) to guide decisions about treatment intensification.

Continuous glucose monitoring (CGM) is one method of identifying such glucose profiles and is measured in mmol/L. Retrospective CGM (r-CGM) involves the patient wearing a CGM sensor for a period of up to 2 weeks and then, usually in collaboration with their health professional, downloading the glucose data to identify day-to-day glucose profiles to guide treatment decisions. For many people with T2D glucose profiles tend to be stable over time and. Therefore. intermittent r-CGM measurements may be sufficient to guide clinical management. r-CGM can also provide detail about hypoglycaemia, hyperglycaemia, glycaemic variability (GV), i.e. the extent to which glucose fluctuates throughout the day as well as time spent in day-to-day glucose target range, all of which may be important to clinical and psychosocial outcomes for people with T2D [12, 13]. R-CGM thus offers the prospect of an advance in appropriate and personalised care for people with T2D [14].

General Practice Optimising Structured Monitoring to Improve Clinical Outcomes in Type 2 Diabetes (GP-OSMOTIC) is a stratified (by GP clinic) individually randomised controlled trial in general practice comparing the use of r-CGM (intervention) to usual care (control) in those with T2D whose HbA1c is above their individualised target level. Within each clinic, participants will be randomly allocated to either the intervention or control group. Full details of the trial method are described elsewhere [15], but are briefly outlined below before presenting the detailed description of the planned statistical methods.

### Primary objective

The primary objective was to assess whether the judicious use of intermittent retrospective continuous glucose monitoring (r-CGM) in people with T2D in primary care improves glycaemic control at 12 months as measured by HbA1c.

### Secondary objectives

Compared with the control arm, does the judicious use of intermittent retrospective continuous glucose monitoring (r-CGM) in people with T2D in primary care:Improve the percentage of time spent in the target glucose range at 12 months?Decrease diabetes-specific distress at 12 months?Result in cost-effective care?Decrease HbA1c at 6 months?

### Primary outcome

The primary outcome measure is the difference in mean HbA1c at 12 months between the intervention and control groups.

### Secondary outcomes

The secondary outcome measures are:Difference in mean percent time in target (4–10 mmol/L) range at 12 months between the study groups (from data downloaded from the r-CGM device).Difference in mean diabetes-specific distress at 12 months between the study groups as measured by the Problem Areas in Diabetes (PAID) scale [16].Incremental cost per quality-adjusted life year (QALY) for the intervention relative to control for the trial period, as measured by the EuroQol 5 dimension 3 levels (EQ-5D-3 L) [17].Difference in mean HbA1c (%) at 6 months between the intervention and control groups.

### Inclusion criteria

Eligible participants will be aged 18–80 years, active patients of the practice (defined as three or more visits to the practice in the last 2 years), have had T2D for at least 1 year with their most recent HbA1c (in the previous 1 month) ≥ 7 mmol/mol (0.5%) above their individualised target (see below) while on at least two non-insulin hypoglycaemic therapy and/or insulin (therapy stable for the last 4 months). Our general glycaemic target is set at 53 mmol/mol (7%) while patients with a history of severe hypoglycaemia (requiring assistance from a third person) or who report impaired awareness of hypoglycaemia (i.e. are unable or have reduced capacity to recognise the early signs and symptoms of hypoglycaemia, which may impede timely self-treatment) will have a target of 64 mmol/mol (8%). In the setting of this pragmatic trial we will allow GPs to indicate a personalised target for a participant if they feel that it should differ from the two pre-specified targets set out above.

Patient exclusion criteria will include: any debilitating medical condition (e.g. unstable cardiovascular disease (CVD), severe mental illness, end-stage cancer), an estimated glomerular filtration rate (eGFR) < 30 ml/min/1.73m^2^, proliferative retinopathy, pregnancy, lactating or planning pregnancy, unable to speak English/give informed consent, unwilling to use r-CGM or follow study protocol, allergy to adhesive tape, diagnosis of T2D within the past 12 months, and any condition that makes monitoring diabetes using HbA1c unreliable (e.g. haemoglobinopathy, iron deficiency anaemia).

### Randomisation

Participants will be stratified by clinic and randomised to either the intervention or control group using randomly permuted block sizes of 4 and 6. The randomisation process will be through REDCap© electronic data capture tools hosted at the University of Melbourne [18], using the application programming interface (API). This allows project information to be exported to a separate statistical computing package which generates allocation sequence tables allowing for random block sizes. These will then be imported back into REDCap© for use through the randomisation graphical user interface (GUI).

### Intervention

In brief, intervention group participants will be asked to wear the r-CGM device for a period of 2 weeks every 3 months, i.e. at baseline, 3, 6, 9, and 12 months, as well as having an HbA1c test at those times, and to attend a consultation with their GP (clinic assessment visit (CAV)) to discuss the r-CGM reports. This 3-monthly interval is in keeping with clinical practice guidelines [19]. Intervention participants will also attend a 60-min education session with the study registered nurse credentialed diabetes educator (RN-CDE) which will include instruction on how to wear the r-CGM device and how to interpret the glucose reports from the device to better understand their blood glucose and how this relates to their diabetes self-management and treatment options. The r-CGM device being used in the study is the Abbott FreeStyle Libre Pro® Flash Glucose Monitoring System.

Control group participants will wear the r-CGM device at baseline (blinded) and thereafter will be managed according to usual clinical care. The GP and patient will be prompted to undertake 3-monthly diabetes reviews in keeping with clinical practice guidelines about step-wise regular consideration of treatment intensification. Patients randomised to the control group will also attend an education session with a local CDE, funded by the study if required to ensure financial barriers do not exist. Control group participants will have an r-CGM sensing at 12 months, which will be used in collaboration with their GP in their management of diabetes after the final HbA1c blood measurement and all other trial outcomes have been collected.

### Outcome measures

The primary outcome, HbA1c, will be measured by venous blood test in an accredited laboratory. Time in the target range will be calculated as the percentage of time blood glucose levels remain between 4 and 10 mmol/L as measured by the r-CGM device. Diabetes-specific distress will be measured using the PAID scale [16]. This scale consists of 20 questions relating to negative emotions associated with diabetes, with five possible responses to each question: 0 = no problem, 1 = minor problem, 2 = moderate problem, 3 = somewhat serious problem, and 4 = serious problem. The 20 items are summed, and the total is multiplied by 1.25 so that total score ranges from 0 to 100. Higher scores indicate greater levels of diabetes-specific distress; a score of ≥ 40 indicates severe diabetes distress [20]. The PAID measure has high internal reliability and validity [16].

Results from the EQ-5D-3 L assessment at each measurement will be transformed into utility scores using Australian preference weights [21]. An average utility curve, which measures the mean quality of life trajectory for patients, will be derived by interpolating between baseline and the follow-up measurement points [22]. QALYs will then be estimated for both the intervention and the control group using the ‘area under the curve’ method [23]. As the economic evaluation will be performed within a 12-month period, discounting will not be applied.

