#### Data collection and preparation

An in-house, web-based, purpose-built recruitment database will be used to document all practices approached to participate in the study. Once consented to the study, REDCap© will be used to store all clinic, GP, and practice nurse (PN) characteristics. All clinic, staff, and participant data will be collected at baseline and 12 months and entered into the database by research assistants using either a desktop computer or tablet. Data from CAVs and any technical issues or adverse events associated with the r-CGM device will be logged by research assistants in REDCap©.

HbA1c data will be collected 6-monthly from the same pathology laboratory for each patient and collated in a Microsoft Excel 2016 file. Participants will be encouraged to have their HbA1c levels collected at 3 and 9 months, but this will not be compulsory. The pathology data will be merged with the clinical patient data in STATA version 15.1 [25].

An in-house, web-based, purpose-built participant tracking database will be used to track changes in patient medication and the progress of patients throughout the study.

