#### Statistical modelling

##### Primary and secondary outcomes

Whilst our primary outcome is HbA1c at 12 months post-intervention, we will estimate the between-group difference in mean HbA1c at 6 and 12 months with the same linear mixed-effects model using restricted maximum likelihood estimation. As the data are longitudinal, HbA1c measured at baseline, 6 months, and 12 months will be included in the model as the dependent variable and study groups (intervention and control) and time of the pathology result (baseline, 6, and 12 months) will be collected as fixed effects. A two-way interaction term between study group and time will be included in the model to estimate the between-group difference in mean HbA1c at 6 and 12 months, but we will constrain the estimated baseline means to be equal. The model will include random intercepts for clinic (as individuals will be clustered within clinics) and individuals (as patient measures are repeated within individuals). An unstructured variance-covariance structure will be assumed for the random effects variables as correlations between measurements within individuals and correlations between measurements in participants from the same clinic are expected to be unique.

Age, index of relative socio-economic disadvantage (IRSD), and a history of severe hypoglycaemia are known to be at least moderately associated with HbA1c [9, 27]. In a secondary analysis, the outcome measure will be adjusted for these potential confounders. These measures will be included as fixed effects in the model.

An intention-to-treat (ITT) approach will be used where participants will be analysed according to the study group they were assigned, and all participants will be included in the analysis, consistent with mixed model analysis [28]. The estimated mean HbA1c levels at baseline, 6 months, and 12 months will be plotted for each study group with 95% confidence intervals.

The same statistical modelling approach described for HbA1c will be used for the secondary outcomes, percentage time in target and diabetes-specific distress at 12 months. Transformations for skewed outcome measures will be considered.

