##### Economic evaluation

A within trial economic evaluation using participants’ Medicare costs, pharmaceutical benefit schedule (PBS) costs, hospitalisation costs, self-reported costs, diabetic outcomes (proportion with controlled diabetes, HbA1c ≤ 7 mmol/mol) and quality of life data will be performed using a decision analytic framework [29]. The economic model will construct costs and quality of life associated with the health states ‘controlled diabetes’, ‘uncontrolled diabetes’, and ‘death’. It will be constructed in STATA statistical software [25] based on the original trial data and will utilise linear and generalised linear modelling techniques to determine a cost per QALY gained. The analysis will be conducted from a health system and societal perspective. Costs and benefits will be bootstrapped. The distribution of costs and benefits will be simulated using a probabilistic analysis. The results of the economic modelling will be presented as the mean and 95% confidence interval (CI) of the incremental cost per QALY gained at trial conclusion for the r-CGM study group relative to the control group. Simulated cost-effectiveness will be presented for r-CGM relative to the control via a cost-effectiveness plane and a cost-effectiveness acceptability curve. Univariate and probabilistic sensitivity analyses will be performed to assess uncertainty. Estimates of projected implementation costs across Australia will be estimated.

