**Table 5 Tab5:** Mean and standard deviation (SD) costs, mean and SD quality-adjusted life years (QALYs), mean differences and incremental cost-effectiveness ratios during the trial follow-up period for intervention vs control groups (secondary analyses)

	Intervention mean (SD)				Control mean (SD)		Mean difference (95% CI) per patient			*P* value
Costs										
Intervention (A)										
Hospital utilization (B)										
Medical benefits (C)										
Pharmaceuticals (D)										
Patient costs (E)										
Total cost health system (A + B + C + D)						(1)				
Total cost societal (A + B + C + D + E)						(2)				
QALYs						(3)				
Incremental cost effectiveness ratio (ICER)										
Health system perspective						(1)/(3)				
Societal perspective						(2)/(3)				

*CI* confidence interval

**Table 6 Tab6:** Estimated glycated haemoglobin (HbA1c) and between-group differences by history of severe hypoglycaemia and personalised HbA1c target for intervention and control groups (sub-group analyses)

	Estimated mean HbA1c (95% CI)				Difference in estimated mean HbA1c and HbA1c target		Unadjusted		Adjusted^a^	
	Intervention group (*n*=)		Control group (*n*=)		Intervention group (*n*=)	Control group (*n*=)	Intervention vs. control between-group differences (95% CI)	*P* value	Intervention vs. control between-group differences (95% CI)	*P* value
Severe hypoglycaemia										
History of severe hypoglycaemia^b^										
Baseline										
6 months										
12 months										
No history of severe hypoglycaemia^c^										
Baseline										
6 months										
12 months										
Personalised HbA1c target										
Personalised target^d^										
Baseline										
6 months										
12 months										
No personalised target^e^										
Baseline										
6 months										
12 months										

*CI* confidence interval

^b^HbA1c target is 8%

^c^ HbA1c target is the general HbA1c target of 7%

^d^ HbA1c target based on average of personalised HbA1c targets

^e^ HbA1c target is the general HbA1c target of 7%

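### The plan names no adjustment of the QALY difference for baseline EQ-5D utility, although baseline utility is part of the area under the curve

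*SAP article*

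**What the plan says.** All references are to the SAP article.

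- **Outcome measures.** EQ-5D-3L responses become utilities ("Results from the EQ-5D-3 L assessment at each measurement will be transformed into utility scores using Australian preference weights"). The average utility curve is "derived by interpolating between baseline and the follow-up measurement points". Then "QALYs will then be estimated for both the intervention and the control group using the" area-under-the-curve method. Baseline utility is thus one end of the curve.
- **Economic evaluation.** The model "will utilise linear and generalised linear modelling techniques to determine a cost per QALY gained". Costs and benefits are bootstrapped. No covariates are named.
- **Table 5.** Its title promises "mean and SD quality-adjusted life years (QALYs), mean differences and incremental cost-effectiveness ratios during the trial follow-up period". The layout has group means (SD) and a single column, "Mean difference (95% CI) per patient". The ICER is the cost row (1) or (2) divided by the QALY row (3).
- **Tables 3, 4 and 6.** Each has separate unadjusted and adjusted columns. Table 5 has neither label.
- **Primary and secondary outcomes.** For HbA1c, "but we will constrain the estimated baseline means to be equal". The same modelling approach is extended to time in target and PAID. It is not extended to QALYs.
- **Data collection and preparation.** "All clinic, staff, and participant data will be collected at baseline and 12 months". EQ-5D times are not listed separately.

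**The concern.** Treatment cannot affect baseline utility. When it forms part of the area under the curve, any chance difference between arms at baseline passes into the QALY difference in two ways: directly, through its weight in the area, and indirectly, because follow-up utility is correlated with it. The QALY difference is row (3) of Table 5, the denominator of both ICERs.

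Randomisation is stratified by clinic only, which does not balance utility. Bootstrapping describes the spread around the estimate but does not remove an imbalance from its centre. Table 2 lists baseline PAID but not baseline utility, so the planned tables would not show an imbalance if one arose.

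Cost per QALY is a listed secondary outcome, and the only one built on a baseline measurement for which the article does not say how baseline is handled in the comparison. At stake are the precision of the QALY difference and how far the ICER depends on chance imbalance.

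**Working it through.** **The plan's own figures.** The article states no utility SD, correlation or target QALY difference, so there is no QALY figure to reproduce. The numbers per arm do reproduce. For a difference of 0.5%, SD 1.3%, significance level 0.05 (taken as two-sided) and power 0.8, the normal approximation gives 107 per group, and the t-test gives 107.09, rounded up to 108. Then 216/0.8 = 270 and 270/0.9 = 300. From 150 per arm, both attrition allowances leave 150 × 0.9 × 0.8 = 108; participant attrition alone leaves 150 × 0.8 = 120.

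**Assumptions (not in the article).** Utility SD σ = 0.15–0.25, equal at each time; correlation ρ = 0.3–0.8; n = 108–120 per arm.

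**Two EQ-5D points (baseline and 12 months).** QALY = (u0 + u12)/2.

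- Variance of a participant's QALY: σ²(1 + ρ)/2.
- Residual variance given u0: σ²(1 − ρ²)/4.
- Ratio, adjusted to unadjusted: (1 − ρ)/2.
- Expected shift in the unadjusted difference per unit of baseline imbalance: (1 + ρ)/2.
- SE of a between-arm difference: √(2 × variance/n).

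With σ = 0.20 and n = 108, one SE of baseline imbalance is 0.20 × √(2/108) = 0.0272, and:

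| ρ | QALY shift at one SE of imbalance | SE unadjusted | SE adjusted | Variance ratio |
|---|---|---|---|---|
| 0.3 | 0.0177 | 0.0219 | 0.0130 | 0.35 |
| 0.5 | 0.0204 | 0.0236 | 0.0118 | 0.25 |
| 0.7 | 0.0231 | 0.0251 | 0.0097 | 0.15 |
| 0.8 | 0.0245 | 0.0258 | 0.0082 | 0.10 |

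Shifts and SEs scale with σ. At ρ = 0.5 and n = 108 the shift is 0.015 for σ = 0.15 and 0.026 for σ = 0.25. Going to n = 120 multiplies shifts and SEs by √(108/120) = 0.95. The variance ratio depends on neither σ nor n.

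For scale, a true 12-month utility effect d adds d/2 to a two-point QALY. A shift of 0.0204 is therefore what a 12-month effect of 2 × 0.0204 = 0.041 would produce, about 0.2 SD at σ = 0.20.

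**Simulation check.** In 4,000 trials with σ = 0.20, ρ = 0.5 and n = 108 per arm, the SE was 0.0236 unadjusted and 0.0119 adjusted (variance ratio 0.25). Baseline imbalance correlated 0.86 with the unadjusted estimate and about 0 (−0.006) with the adjusted one.

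**Three points (6 months added).** The trapezoid weights are 1/4, 1/2, 1/4. With equal correlations, in units of σ², the QALY variance is 0.375 + 0.625ρ and the covariance with baseline is 0.25 + 0.75ρ. The residual variance is the first minus the square of the second.

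| ρ | QALY variance | Residual variance | Ratio |
|---|---|---|---|
| 0.3 | 0.5625 | 0.3369 | 0.60 |
| 0.5 | 0.6875 | 0.2969 | 0.43 |
| 0.7 | 0.8125 | 0.2119 | 0.26 |

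The variance reduction is then about 40%, 57% and 74%.

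**The case against.** **The plan does not say the comparison is unadjusted.** A reader might infer that a raw difference has been specified. The documents do not support that. Outcome measures describes how QALYs are built, not how the arms are compared; Table 5 labels its difference neither way; and the regression in Economic evaluation could carry baseline utility. This stands, so the point is that no adjustment is specified. It does not dispose of the point. The article sets out intended table layouts, labels adjustment in every other results table with between-group differences, and says its analyses are pre-specified. Here it leaves the choice open.

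**An article condenses.** A covariate list for an economic analysis might sit in a fuller document. That is fair, and one sentence would settle it. But the baseline handling of the other outcomes is stated here, so its absence for QALYs is a visible asymmetry.

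**The estimator may differ.** The same section describes a decision-analytic model with health states. If the QALY difference comes from that model, the two-point formula may not describe it exactly. This stands as a limit on the figures. Table 5 nevertheless reports participant-level QALY means and SDs and forms the ICER from their difference.

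**There is no bias.** One might infer that the QALY result would be invalid. It would not be: under randomisation the unadjusted difference is unbiased on average, and its bootstrap interval already reflects baseline variability. What remains is error conditional on the imbalance that occurs, and lost precision.

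**The size is assumed.** The SD, the correlation and the EQ-5D times are all assumptions. The general statement on participant data points to two measurements, while the plural for follow-up measurement points leaves room for more. Both cases are therefore shown.

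**Conclusion.** The concern holds in this form: baseline utility is inside the QALY outcome, and nothing in the article adjusts the between-arm QALY difference for it, unlike HbA1c, time in target and PAID. If the analysis follows the layout as printed, chance baseline imbalance enters the ICER denominator and precision is given up.

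Under the stated assumptions, adjustment reduces the variance of the QALY difference by about 65–90% with two EQ-5D points (ρ 0.3–0.8), or about 40–74% with a 6-month point as well (ρ 0.3–0.7). The size depends on the assumed correlation and number of measurements. In the two-point case the direction does not: for any ρ of 0 or above, the variance at least halves.

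A reader might go further and conclude that imbalance would match or reverse the true QALY gain. That needs a figure for the expected gain, which the article does not give. The primary HbA1c analysis and the sample size are unaffected. This is a worthwhile improvement to one secondary outcome, not a fault in the trial's main inference.

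**What to change.** Add to Economic evaluation:

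- Compute QALYs per participant and estimate the between-arm difference by regression on arm with baseline EQ-5D utility as a covariate.
- If clinic is included, enter it as a random effect, in line with the reasoning in the Discussion. Fixed effects for 50 clinics of about six participants would add up to 49 terms.
- Fit this regression within each bootstrap replicate.
- Use the adjusted difference as (3) in Table 5 and in both ICERs, and label it as adjusted. The unadjusted difference can be shown beside it, as in Tables 3 and 4.
- State the EQ-5D time points, and add baseline utility to Table 2.
- If the QALY difference is to come from the health-state model, say so and say how baseline utility enters it.

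The cost is a few sentences, one covariate and a table label. Baseline EQ-5D is already required for the utility curve, so no new data are needed. If adjustment is already intended, stating it closes the point.
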